## Concomitant medications

### Corticosteroids

All participants will receive corticosteroids for the first 8 weeks of TBM treatment as used in a randomised controlled trial demonstrating mortality benefit in patients TBM
^
5
^.

### Antiretroviral therapy (ART)

ART will be commenced by treating clinicians after 4–6 weeks of antitubercular therapy in all participants based on the single randomised controlled trial of ART timing in TBM, which showed no benefit for earlier ART
^
40
^. If available, a dolutegravir-based regimen will be used in accordance with international
^
41
^ and local guidelines
^
42
^.

### Gastric protection

Participants can be prescribed omeprazole 40mg daily. A higher starting dose of 40mg OD was selected to account for the interaction between proton pump inhibitors (PPI) with rifampicin via CYP2C19 and CYP3A4 leading to reduction in levels of the PPI. In participants with persistent symptoms the dose will be titrated to 80mg daily and gastroscopy considered. Although the study initially planned to use ranitidine for this indication, this was withdrawn as a concomitant medication due to concerns over a potential contamination with the probable carcinogen N-nitrosodimethylamine (NDMA)
^
43
^, making the medication unavailable for use in South Africa. 

### Pyridoxine

Participants will receive pyridoxine supplementation as per the South African guidelines for prevention of anti-tuberculosis drug-related peripheral neuropathy
^
44
^.

### Disallowed medications

The medicines listed in
Box 3 have been shown to interact with study drugs and are therefore contraindicated for concomitant use during the study.

Box 3. Contraindicated medications for study participants
**Tricyclic antidepressants:** Amitriptyline, Amoxapine, Clomipramine, Desipramine, Doxepin, Imipramine, Nortriptyline, Protriptyline, Trimipramine.
**Selective Serotonin Re-uptake Inhibitors (SSRI’s):**
Citalopram, Escitalopram,
Fluoxetine, Fluvoxamine, Paroxetine, Sertraline. Serotonin-Noradrenaline Re-uptake Inhibitors (SNRI’s) Venlafaxine, Duloxetine, Levomilnacipran, Milnacipran.
**Serotonin Receptor Agonist**, Buspirone,
**Mono-amine Oxidase Inhibitors (MOAIs**), Isocarboxazid, Nialamide, Phenelzine, Tranylcypromine, Selegiline, Rasagaline, Toloxatone.
**Reversable MOA Inhibitors (RIMAs):**Moclobemide, Pirlindole.
**Migraine medications**: Triptans.
**Macrolide antibiotics**:
Clarithromycin,
Erythromycin, Troleandomycin.
**Opiate analgesics**: Methadone,
Tramadol, Pentazocine.
**Stimulants**: MDMA (ecstacy), Cocaine,
Methamphetamine
**Hormonal treatment**:
Gestodene, Testosterone.
**Other medications**: Antiretrovirals –
Atazanavir, Anti-arrhytmic – Quinidine, Anti-malarial – Quinine, Chemotherapy – Doxorubicin, Asthma –Furafylline, Hypertension – Hydracarbazine, Antifungal – Ketokonazole, Amino-acid - Tyramine
**Bold** represents class of drug.
Underlined medications represent commonly used medications in South Africa.

## Study procedures, schedule and clinical assessments

Participants will undergo six scheduled study visits after screening, plus ascertainment of vital status and disability assessment at 6 months.
Table 4 describes planned investigations at each study visit.

**Table 4. T4:** Planned study assessments and procedure per study date.

Visit (window in days)	SCR	ENR	Day 3 (+/- 1)	Day 7 (+/- 2)	Day 14 (+/- 2)	Day 28 (+/- 3)	Day 56 (+/- 4)	Day 180
**Bedside**								
Study Informed Consent	x	x						
Vital Signs	x	x	x	x	x	x	x	
Medical History	x	x	x	x	x	x	x	x
Physical Examination	x	x	x	x	x	x	x	
BPNS and mTNS	x							
Modified Rankin Score		x		x	x	x	x	x
Insomnia Questionnaire						x	x	
MOCA, IHDS, EQ5d5L							x	
Neurocognitive mini-battery								x
AE/SAE, Adherence Monitoring		x	x	x	x	x	x	
Randomisation and treatment assignment		x						
**Blood**								
Weight		x	x	x	x	x	x	
Haematology: FBC and white cell differential								
Biochemistry: Creatinine, eGFR, electrolytes, LFTs	x		x	x	x	x	x	
INR	x		x			x		
HIV-1 ELISA +/- HIV Rapid Test (x2) if required	x							
CD4+ count, HIV Viral Load		x						
Plasma for PK sub-study (sparse sampling)						x	x	
Plasma for PK sub-study (intensive sampling – if consented)			x					
Stored plasma for immunological, proteomic and metabolomic profiling		x	x	x	x	x	x	
PBMC for storage		x	x			x		
Whole blood for RNA extraction		x	x	x	x	x	X	
Whole blood for DNA extraction (if consented)		x						
**Urine**								
Urine for pregnancy test	x							
Urine for storage		x			x		x	
**Cerebrospinal Fluid Analysis**								
Cell count, MC+S, TB culture, GeneXpert Ultra (inc Rif resistance)			x			x		
Biochemistry: protein and glucose			x			x		
Stored CSF for immunological, cellular, proteomic and metabolomic profiling;			x			x		
CSF for RNA extraction								
CSF for PK sub-study			x			x		
**Imaging**								
MRI Head, or CT Head if MRI not tolerated (+/- 5 days)		x					x	

SCR: Screening; ENR: Enrolment; AE: Adverse Event; BPNS: Brief Peripheral Neuropathy Score; CSF: Cerebrospinal Fluid; CT: Computerised Tomography; FBC: Full Blood Count; LFT: Liver Function Tests; IHDS: International HIV Dementia Score; MC+S: microscopy, culture and sensitivity; MOCA: Montreal Cognitive Assessment; mTNS: modified Total Neuropathy Score; MRI: Magnetic Resonance Imaging; PAOFI: Patients Assessment of Own Functioning Inventory; PBMC: Peripheral Blood Mononuclear Cells; PK: Pharmacokinetic;.

### Clinical assessment

Clinical assessment will include clinical history, conscious level by GCS, presence of new or ongoing focal neurological deficit, all adverse events, new medications started and adherence to drugs. The neurological examination at D180 is extended to assess for such as language, visuospatial deficit, visual agnosia and praxis: focal neurocognitive deficits which may be present in people with TBM.

### Modified Brief Peripheral Neuropathy Score

This purely clinical early screening tool was adapted from the subjective peripheral neuropathy score (SPNS) validated for the assessment of HIV associated distal sensory polyneuropathy (DSP)
^
45
^ and used previously in trials to assess LZD toxicity.

### Modified Total Neuropathy Score

This screening tool, initially developed for the assessment of chemotherapy induced neuropathy
^
46
^, has been modified for use in the HIV research setting where it has shown acceptable sensitivity and specificity (85% and 80% respectively)
^
47
^. Prior studies have used a simplified 16-point
^
48
^ or 20-point clinical scoring system
^
49
^ as markers of HIV-associated DSP severity.

### Insomnia Severity Index

All participants will complete the Insomnia Severity Index (ISI) at the Day 28 and 56 visits. The ISI is a brief screening measure of insomnia which has been validated for use in insomnia research
^
50
^. Dolutegravir has been associated with neurotoxicity presenting with neuropsychiatric symptoms such as insomnia
^
51
^, and this will be assessed as part of the PK/PD assessment.

### Measures of neurocognitive function

These measures where possible will be done in the participants preferred language.

*i) Montreal Cognitive Assessment*
The Montreal Cognitive Assessment (MoCA) assesses six broad domains of ability and neurocognitive function
^
52
^ and has been used to screen for cognitive impairment in previous studies within South Africa
^
53
^. This will be carried out at day 56 and day 180.
*ii) Cognitive Assessment Tool-Rapid Version (CAT-Rapid).*
This instrument includes four questions about subjective cognitive complaints, as well as tasks assessing learning and memory and cognitive sequencing. CAT-rapid was developed in South Africa (Joska
*et al*., 2016), in response to the need to develop a brief screening tool that includes functional symptom questions and a measure of executive function. The CAT-rapid incorporates aspects of the International HIV Dementia Scale and includes four symptom questions, as well as tasks assessing learning and memory and cognitive sequencing.
*iii) Brief neuropsychological battery*
Neuropsychological testing will be carried out by a trained neuropsychometric tester and clinical research worker at day 180 and will include a neurocognitive test battery and assessment of contributing mental health symptoms. The neurocognitive battery comprises 12 standardised tests, each of which assesses performance in one of six cognitive domains commonly affected by TBM. The domains, tests, and outcome variables are: (1) Executive Functioning: Color Trails Test 2 (CTT2) - completion time; Wisconsin Card Sorting Test (WCST) - perseverative errors; (2) Learning and Memory: Hopkins Verbal Learning Test-Revised (HVLT-R) - total learning total and delayed recall total; Brief Visuospatial Memory Test-Revised (BVMT-R) - total learning total and delayed recall total; (3) Generativity/fluency: category fluency - total number of animals / total number of fruits and vegetables named in 1 minute; (4) Attention/Working Memory: Wechsler Adult Intelligence Scale-Third Edition (WAIS-III) Digit Span - total score; (5) Processing Speed: CTT1 - completion time; Wechsler Adult Intelligence Scale-Third Edition (WAIS-III) Digit Symbol Coding - total score; WAIS-III Symbol Search- total score; (6) Motor Function: Grooved Pegboard Test (GPT) dominant (DH) and nondominant hand (NDH) - completion time; Finger Tapping Test (DH and NDH) - completion time. Tests were administered in either English or Xhosa depending on the participant’s preference. Mental Health measures are the Centre for Epidemiological Studies-Depression (CES-D), State Trait Anxiety Inventory-trait (STAI-trait), Alcohol Use Disorders Identification Test (AUDIT) and Drug Use Disorders Identification Test (DUDIT).

### Measures of functional status

*i) Modified Rankin Score*
The MRS, a commonly used clinical outcome measure for patients suffering from stroke
^
54
^, has demonstrated good inter-rater reliability
^
55
^ and is the most commonly used outcome measure to assess neurological disability in TBM
^
56
^.
*ii) Modified Patients Assessment of Own Functioning Inventory (PAOFI)*
This patient reported outcome measure is designed to evaluate a patient’s sense of his or her functional capacity in everyday activities concerning memory, language and communication, use of hands, sensor perception, higher level cognitive and intellectual functions, and work/recreation
^
57
^.
*iii) Lawton Instrumental Activities of Daily Living-South Africa*
This test is designed to assess independent living skills, considered more complex than basic activities of daily living. This was developed in 1969
^
58
^, but since modified for use in the South African context
^
59
^.

### Blood

Testing will be done at specified timepoints (as per
Table 4), and may be repeated to follow-up on abnormal results, for example after occurrence of an AE. Samples for haematology and biochemistry and HIV testing will be processed in National Health Laboratory Service (NHLS) laboratory according to local SOPs. Samples for non-clinical assays (immune markers, RNA, metabolomics, proteomics) and future use will be collected and transported to the Institute of Infectious Disease and Molecular Medicine at the University of Cape Town (UCT) for processing and storage. PK samples will be centrifuged
*within an hour* of being taken at 1500 x g at room temperature for 10 minutes, the plasma aliquoted into cryovial tubes, stored at -80ᵒC and transported to UCT Clinical Pharmacology laboratory for storage and processing.

### Urine

Bedside pregnancy testing will be done on urine at screening. Urine will be sent to chemistry laboratories for osmolality and electrolyte testing in the context of hyponatraemia at the discretion of the investigator. Further urine will be collected for biobank storage.

### Cerebrospinal fluid analysis

CSF will be obtained via lumbar puncture at Days 3 and 28, in accordance with a detailed SOP. CSF collected for diagnosis in routine care (baseline) will be retrieved where possible. Routine microbiology, cell count, and biochemistry will be done in NHLS laboratory according to local SOPs. Samples for non-clinical testing (RNA sequencing, metabolomic and proteomic analysis and immunological assays) will be collected and transported to the IDM at UCT for processing and storage. CSF to determine drug concentrations for the PK study will be frozen at -80 degrees immediately following collection and transported to UCT Clinical Pharmacology laboratory for storage and processing.

### Magnetic resonance imaging (MRI)

MRI scans will be performed in all participants who can tolerate or access the investigation at baseline and day 56. A 3-Tesla (3T) MRI scanner located at Groote Schuur Hospital will be used for all imaging in the Cape Town area, whilst a 1.5T scanner located at Livingstone Hospital will be used for participants recruited in the Port Elizabeth Area. Gadolinium enhanced imaging will be performed on participants with eGFR < 30mL/min/1.73m
^2^.

Image sequences will include the following:

• T1 weighted sequences with or without gadolinium

• T2 weighted sequences

• Diffusion weighted images (DWI)

• Susceptibility weighted images (SWI)

• T2 Fluid-attenuated inversion recovery (FLAIR)

• Point resolved spectroscopy (PRESS/MEGA-PRESS) to estimate brain metabolite changes

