**Exclusion criteria**
•   Rifampicin-resistant
*M.tb* detected on any clinical specimen;•   History of allergy or hypersensitivity to RIF, isoniazid, ethambutol, pyrazinamide, LZD or ASA;•   Received more than 5 days of antitubercular therapy in the 30 days prior to screening;•   Receipt of regular daily ASA or NSAID prior to TBM diagnosis•   CSF unobtainable by lumbar puncture or another procedure;•   Evidence of bacterial or cryptococcal meningitis;•   Severe concurrent uncontrolled opportunistic infection including, but not limited to, active cytomegalovirus-associated disease, Kaposi sarcoma,
*Pneumocystis jirovecii* pneumonia, HIV related or unrelated malignancy, or gastrointestinal bleeding;•   Any other form of immunosuppressive therapy, including antineoplastic and biologic agents, apart from corticosteroids;•   More than 17 weeks pregnant at baseline;•   Peripheral neuropathy scoring Grade 3 or above on the BPNS;•   Any disease or condition in which the use of the standard anti-TB drugs (or any of their components) are contraindicated. This includes, but is not limited to, allergy to any TB drug or their components;•   The presence of one or more of the following:-   Estimated glomerular filtration rate (eGFR) < 20ml/min/1.73 m2
*
-   INR > 1.4 and/or clinical evidence of liver failure or decompensated cirrhosis;-   Haemoglobin < 8.0 g/dL;-   Platelets < 50 x109 /L;-   Neutrophils < 0.5 x 109 cells/L;•   Any disease or condition in which any of the medicinal products listed in the section pertaining to prohibited medication (See
Box 1) is used and cannot be safely stopped;•   Known or suspected history of drug abuse or any other reason that is, in the opinion of investigators, sufficient to compromise the safety or cooperation of the participant.*Calculated using the Cockcroft-Gault equation; INR: International normalised ration; BPNS: Brief peripheral neuropathy score; NSAID: Non-steroidal anti-inflammatory drug.

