### Computed tomography (CT)

If participants are unable to tolerate or access MRI, CT will be used as an alternative imaging method at the same time points as stated for MRI. Participants with eGFR > 30 mL/min/1.73m
^2^ will have contrast enhanced imaging. Pre- and post- contrast sequences will be available for analysis. A standardised reporting form including positive and negative radiological findings will be used. 

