## Version control

Submitted version of the protocol: V6 (dated 11 May 2020).

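### The MRI section directs gadolinium to eGFR below 30 while the CT section directs contrast to eGFR above 30; the MRI inequality sign is most likely reversed

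*Protocol article*

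**What the plan says.** Four places in the protocol article bear on this.

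- **Magnetic resonance imaging (MRI):** "Gadolinium enhanced imaging will be performed on participants with eGFR < 30mL/min/1.73m"². The sequence list in the same section includes "T1 weighted sequences with or without gadolinium", so enhanced and unenhanced scans are both expected.
- **Computed tomography (CT):** where MRI cannot be tolerated or accessed, "CT will be used as an alternative imaging method at the same time points as stated for MRI". Contrast is then given by renal function: "Participants with eGFR > 30 mL/min/1.73m"² are to have enhanced CT.
- **Box 2, Exclusion criteria:** "Estimated glomerular filtration rate (eGFR) < 20ml/min/1.73 m2" excludes a patient, so participants enter with eGFR 20 or above.
- **Table 4:** brain imaging is planned at enrolment and day 56. The row "Biochemistry: Creatinine, eGFR, electrolytes, LFTs" is marked at screening and at days 3, 7, 14, 28 and 56.

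**The concern.** Two adjacent rules for giving contrast use the same threshold and the same units but point in opposite directions. They serve the same imaging assessment at the same two time points, and which one applies to a participant depends only on whether MRI is feasible.

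Taken literally, the only eligible participants whom the MRI rule positively sends for gadolinium at baseline are those with the poorest renal function the trial accepts, while the CT rule leaves that same group out of its contrast instruction. The matter is one of clinical operation and possibly of participant safety. It also leaves unclear which MRI scans are meant to be enhanced, and these scans feed a secondary aim and the secondary endpoint on MRI and CT changes at day 56.

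**Working it through.** No figure in the protocol has to be reproduced. The check sets the rules side by side and works out which eGFR values each one names.

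**Inputs** (eGFR in mL/min/1.73 m²)

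- Entry (Box 2): eGFR ≥ 20.
- MRI rule: gadolinium if eGFR < 30.
- CT rule: contrast if eGFR > 30.

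**Values named for contrast at baseline**

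| eGFR | MRI, as written | CT, as written | MRI, with the sign reversed |
|---|---|---|---|
| 20 to < 30 | named | not named | not named |
| exactly 30 | not named | not named | not named |
| > 30 | not named | named | named |

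1. The MRI rule combined with the entry limit gives 20 ≤ eGFR < 30, a band of 30 − 20 = 10 units.
2. The CT rule gives eGFR > 30.
3. The overlap of < 30 and > 30 is empty: no eGFR value is named by both rules.
4. Reversing the MRI sign gives eGFR > 30, which is identical to the CT rule.

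The entry limit applies at enrolment only. At day 56 the MRI rule as written names anyone below 30, with no lower bound.

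Not named means that the rule gives no instruction; it is not a prohibition. The MRI sentence does not say that only this group may have gadolinium, and the sequence list allows T1 imaging either way.

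**Could the two directions be deliberate?** A complementary scheme, with gadolinium MRI for those who should not have CT contrast, would require renal function to decide between the modalities. It does not. The CT section makes CT the fallback for intolerance or lack of access, and the imaging row of Table 4 likewise ties CT to MRI not being tolerated. MRI is the default for everyone who can have it, whatever their eGFR.

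**Could it be a fault in reading the text?** This is unlikely. Both signs are printed, and the `<` and `>` signs in the exclusion criteria and the CT section read sensibly.

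**The case against.** The strongest reply is that this is a small editorial slip. The two rules govern different modalities, so a site could follow both without a logical clash. The article does not say that gadolinium is hazardous at low eGFR, nor why CT contrast is limited to eGFR above 30, so the safety reading is not established by the text. The primary endpoint is solicited adverse events and death, to which this rule makes no difference. The article condenses a fuller document ("Submitted version of the protocol: V6 (dated 11 May 2020"), and if the slip is confined to the article no site is following it. Finally, a dropped negative (gadolinium *not* to be given below 30) would explain the sentence as well as a reversed sign.

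Much of this stands. No harm is shown, the cause is inferred, and the operational consequence depends on a document not available here. It does not remove the discrepancy. The sentence is a stated instruction in the methods, not a detail left to another document, and nothing in the article reconciles it with its neighbour. The two candidate causes lead to almost the same corrected rule, differing only at exactly 30. That the rules can both be followed does not explain why a substitute scan should be enhanced in the opposite renal group.

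**Conclusion.** The concern holds. The MRI contrast rule is very probably wrong as written and should be corrected. That the two rules point in opposite directions is certain; that the cause is a reversed sign is the most likely explanation, not a proven one.

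In size, the baseline rule names a band 10 mL/min/1.73 m² wide (20 to below 30). How many participants fall in it cannot be said, because the article gives no eGFR distribution. There is no effect on the primary endpoint and no shown bias between arms. The safety implication is possible, not demonstrated. It becomes a practical matter only if protocol V6 or the site instructions carry the same sign.

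**What to change.** 1. Check the sign against protocol V6 with the clinical and radiology leads.
2. In the MRI section, change `<` to `>`. If `≥` is preferred, use it in the CT section as well, so that both rules share one boundary and an eGFR of exactly 30 is covered.
3. Only if V6 or site instructions carry the `<` sign: correct them, notify the sites, and check gadolinium use in scans already done in participants with eGFR below 30. Table 4 schedules eGFR at screening and day 56, which serves both imaging time points, so these participants can be identified from data already planned for collection. Whether gadolinium was given may have to come from radiology records, since the article does not show that it is recorded as trial data.

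**Cost.** If the error is only in the article, a one-character correction. If V6 has it too, a protocol amendment, which under the amendment policy needs approval before use (with an exception where a participant's safety is judged to be compromised), plus a note to sites and a check confined to participants below 30. The article reports 52 enrolled of up to 100, so at that date up to 100 − 52 = 48 further participants could still benefit from a corrected rule.

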### Computed tomography (CT)

If participants are unable to tolerate or access MRI, CT will be used as an alternative imaging method at the same time points as stated for MRI. Participants with eGFR > 30 mL/min/1.73m
^2^ will have contrast enhanced imaging. Pre- and post- contrast sequences will be available for analysis. A standardised reporting form including positive and negative radiological findings will be used. 

## Statistical considerations

### Sample size

The total number of participants required for primary safety analysis is 100. This encompasses:

Arm 1 - control - (standard-of-care): 40

Arm 2 - experimental - (standard-of care + high dose rifampicin + linezolid): 30

Arm 3 - experimental - (standard-of care + high dose rifampicin + linezolid + aspirin): 30

### Sample size justification

This phase IIA trial will focus on evaluating adverse events in the experimental arm relative to the standard of care arm. Solicited treatment related AE (
Table 1) plus deaths will be evaluated, and the Data Safety Monitoring Board (DSMB) will provide recommendations accordingly. The DSMB will review all safety events and approve the ongoing conduct of the trial. Analyses that will aid their decision-making will be based on several sources: 

First, a test of proportions will compare the AE rates between the standard-of-care arm and the experimental arms. Concerns about a worse safety profile will be flagged using a two-sided type I error rate of 0.1. Consider a scenario in which there are 10 out of 20 AE in the standard-of-care arm and 14 out of 20 in the experimental arms. This corresponds to a two- sided p-value of 0.053 using Boschloo’s test and would be reason for the DSMB to consider stopping the trial. 

Similarly, a Bayesian posterior probability (with an uninformative prior) of the probability that the AE rate in the experimental arm is worse than that in the control arm. This will provide an additional means of interpreting the relative results. If this probability is high, the DSMB may recommend stopping the study. For example, in the 10/20 and 14/20 scenario the posterior probability that the experimental arm has a worse rate of AEs is 94%. If the split was 10/20 versus 14/20, this probability would be 89%. The DSMB will be unblinded to safety data after every 15 patients recruited (5 per arm). At each point, absence of a significant safety signal (as outlined in the DSMB charter) will permit ongoing recruitment.

Although there is no power calculation to justify the primary outcome due to the complexity of multiple adverse events of special interests, it was felt that recruitment of up to 100 participants will allow sufficient numbers to permit calculations as detailed above and in doing so reveal a signal in terms of the safety of use of the three investigational products. Further detail is provided in the statistical analysis plan included as extended data
^
34
^.

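### The worked example for the DSMB safety flag is wrong: 10/20 versus 14/20 gives a two-sided Boschloo p of 0.23, not 0.053, and the same split is given posteriors of both 94% and 89%

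*Protocol article*

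**What the plan says.** All the statements are in the Protocol article under Sample size justification.

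- The flag: "Concerns about a worse safety profile will be flagged using a two-sided type I error rate of 0.1".
- The example: "10 out of 20 AE in the standard-of-care arm" against "14 out of 20 in the experimental arms".
- The p-value given to it: "This corresponds to a two- sided p-value of 0.053 using Boschloo’s test". This result "would be reason for the DSMB to consider stopping the trial".
- The Bayesian companion, under an uninformative prior whose form is not stated: "in the 10/20 and 14/20 scenario the posterior probability that the experimental arm has a worse rate of AEs is 94" per cent.
- The sentence directly after that: "If the split was 10/20 versus 14/20, this probability would be 89" per cent.

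No cut-off is given for the posterior probability; the text says only that a high value may lead the DSMB to recommend stopping. The same section presents these analyses as aids to the board's decisions and refers to the DSMB charter for what counts as a significant signal. The section Pausing and stopping rules also leaves the halting rules to the charter.

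**The concern.** Two things look wrong on reading. First, one split cannot have two posterior probabilities under one prior, yet consecutive sentences give 10/20 versus 14/20 first 94% and then 89%. The wording of the second sentence suggests a contrast with a different split, so at least one set of counts appears to be misprinted. Second, a difference of 50% against 70% with 20 per arm is too small to give a two-sided p-value near 0.05.

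What is at stake is how the safety flag is understood. The section gives no power calculation for the primary outcome and rests the adequacy of up to 100 participants on being able to make calculations of this kind. The example is where a reader learns how large an imbalance the flag would pick up. As printed, it suggests that an excess of four events in 20 would be flagged. If that is untrue, the example overstates the sensitivity of the monitoring, which is the reassuring direction in a safety trial. Under Study status the article reports 52 participants enrolled, with DSMB reviews after every 15, so monitoring is under way.

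**Working it through.** **Inputs from the document:** 20 per arm; control 10 events; experimental 14 events; Boschloo's test, two-sided; flag at 0.1; printed results p = 0.053, posterior 94% and posterior 89%.

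**Assumption:** the prior is described only as uninformative. A uniform Beta(1,1) prior on each rate is used, with Jeffreys Beta(0.5,0.5) as a check.

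**Step 1: p-value.** Boschloo's test orders all 2×2 tables by their Fisher p-value, sums the probability of tables at least as extreme as the one observed, and takes the maximum over the common event rate π:

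p = max over π of Σ Bin(i; 20, π) × Bin(j; 20, π), summed over all (i, j) with Fisher p(i, j) ≤ Fisher p(observed).

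For 10/20 versus 14/20 the two-sided Fisher p is 0.333. The maximum is reached at π ≈ 0.34 and gives p = 0.2275. A library routine and a separate grid maximisation agree. The printed 0.053 is not reproduced: 0.2275 / 0.053 ≈ 4.3.

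**Step 2: could another method give 0.053 for these counts?**

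| Method, 10/20 v 14/20 | p |
|---|---|
| Boschloo, one-sided | 0.114 |
| Barnard, two-sided | 0.231 |
| Fisher, two-sided | 0.333 |
| Chi-square, without / with continuity correction | 0.197 / 0.333 |
| Wald | 0.187 |
| Boschloo two-sided, both experimental arms pooled at 28/40 | 0.143 |

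None comes near 0.053, and every one exceeds 0.1.

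**Step 3: posterior probability.** With x events in 20 and a Beta(1,1) prior, each rate has posterior Beta(x + 1, 21 − x). The quantity is P(p_exp > p_ctl) with p_ctl ~ Beta(11, 11) and, for 14 events, p_exp ~ Beta(15, 7). Integration gives 0.896 (Jeffreys 0.902). The printed 89% is therefore right for 14/20 if truncated (90% if rounded); the printed 94% is not.

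**Step 4: which split does each printed figure fit?** Control is 10/20 throughout.

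| Experimental | Two-sided Boschloo p | Posterior, uniform prior (Jeffreys) | p below 0.1? | Printed figure that fits |
|---|---|---|---|---|
| 14/20 | 0.2275 | 89.6% (90.2%) | No | 89% |
| 15/20 | 0.117 | 94.5% (94.9%) | No | 94% |
| 16/20 | 0.0533 | 97.4% (97.8%) | Yes | 0.053 |

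The three printed results match three different counts, all labelled 14/20. Changing one digit does not repair the text: reading 16/20 in the first scenario keeps 0.053 but makes the posterior 97%, and reading 15/20 keeps 94% but makes p 0.12 and removes the flag.

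**The case against.** The strongest reply is that this is only an illustration. The quantitative statement is the two-sided 0.1 level in the sentence before it, which the misprint does not touch. The analyses are described as aids, the stated consequence is that the board may consider stopping, and the halting rules belong to the charter. An independent statistician prepares the DSMB data, and a board given correctly computed p-values would not treat 14/20 as flagged. The primary analysis (Wilson intervals, Fisher's exact test) does not use the example, and the sample size does not follow from it by a power calculation. All of this stands. It limits the consequence of the error but does not make the figures right: the example still gives the wrong answer against the plan's own level and contradicts itself.

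A reader might infer more than the document supports:

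- **That the DSMB is working to a wrong stopping rule.** The charter is not shown, so whether it carries the same example is unknown.
- **That the p-value and the posterior disagree as tools**, because 15/20 gives 94% but is not flagged. That sets a two-sided p against a one-directional probability. At 15/20 the one-sided Boschloo p is 0.059 and one minus the posterior is 0.055, so they agree closely. With no posterior cut-off stated, 94% cannot conflict with the absence of a flag.
- **That flagging always needs an excess of six events.** This holds only for 20 per arm with exactly 10 control events.
- **That the false-flag rate is badly inflated.** The 0.1 level is applied at repeated looks, so the cumulative chance of a flag does exceed the per-look level. Its size depends on assumptions the article does not settle, such as whether the arms are tested separately or pooled and how complete outcomes are at each look. An unadjusted, sensitive flag is a defensible choice for an advisory safety review.

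**Conclusion.** The concern holds for the worked example. For 10/20 versus 14/20 the two-sided Boschloo p is 0.23, not 0.053. This reverses the example, because the split does not reach the stated 0.1 level; with 20 per arm and 10 control events, the smallest experimental count that does is 16/20. The same split is also given two posteriors, of which 89% is right to within truncation and 94% is wrong.

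The p-values rest only on the printed counts and the named test. The posteriors assume a uniform prior; Jeffreys priors move them by less than one percentage point and do not bring 14/20 to 94%. The document does not show whether the counts or the results were misprinted. The 0.1 level is unchanged, so the correction makes the flag neither more nor less sensitive; it only describes it accurately. No effect on the charter or on any DSMB decision has been shown.

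**What to change.** Reconcile the counts, the p-value and the posteriors in Sample size justification with the SAP and the DSMB charter, and replace the example with:

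| Control | Experimental | Two-sided Boschloo p | Posterior that experimental is worse | Flagged at 0.1? |
|---|---|---|---|---|
| 10/20 | 14/20 | 0.23 | 90% | No |
| 10/20 | 15/20 | 0.12 | 94% | No |
| 10/20 | 16/20 | 0.053 | 97% | Yes |

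State that the posteriors use uniform Beta(1,1) priors. Attach the remark about considering stopping only to a split that reaches the flag. Send the corrected table to the DSMB in a short memo and confirm that the charter does not contain the wrong split.

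Optionally, call 0.1 a nominal level per look, since it is applied at repeated reviews. This is a wording preference and not part of the required correction.

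The cost is one corrected paragraph, one memo and one check of the charter. No participants, procedures or analyses are added, and the flag level stays as it is.
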